**Figure 3 F3:**
[figure not shown]
**Algorithm for the titration of insulin in the tight control group**.

The protocol for glucose control in group 2 has been carefully designed to achieve tight glucose control whilst minimizing the risk of hypoglycaemia, the principal side effect of insulin therapy. Standard insulin solutions will be used and changes in insulin infusion rates will be guided both by the BG and its rate of change from previous measurements. BG levels will be routinely measured as in all PICUs using commercially available 'point of care' analysers which utilise very small blood samples, producing results in approximately 1 minute. Analysers are rigorously maintained and subjected to laboratory-standard quality assurance programmes.

Training in use of the BG control protocol will be provided before the first patient is enrolled in each collaborating centre and for new staff throughout the trial. The Clinical Co-ordinating centre team will liaise closely with local clinicians to ensure that BG control algorithms are followed closely and safely.

### Outcome measures

#### Primary outcome

Following the influential ARDSNET study[50] the primary outcome for CHiP trial is the number of days alive and free from mechanical ventilation within the 30 days after trial entry. Death is obviously an important outcome. Mechanical ventilation can be seen as a measure of disease severity, defining the need for complex intensive care. The concept of ventilator free days (VFDs) brings together these two outcomes. Schoenfeld[51] define VFDs as: VFD = 0 if the child dies before 30 days; VDF = (30-x) if the child is successfully weaned from ventilator within 30 days (where × is the number of days on ventilator); or VFD = 0 if the child is ventilated for 30 days or more. The use of organ failure free days to determine patient-related morbidity surrogate end-points in paediatric trials has been supported by influential paediatric trialists in the current low mortality paediatric critical care environment[52].

#### Secondary outcomes

Death within 30 days after trial entry (or before discharge from hospital if duration is greater than 30 days)

Death within 12 months of trial entry

Number of days in PICU

Duration of mechanical ventilation

Duration of vasoactive drug usage (adrenaline, noradrenaline, dopamine, dobutamine, or Phoshopdiesterase type III [PDEIII] inhibitors or vasopressors)

Need for renal replacement therapy

Blood stream infection (positive cultures associated with two or more features of systemic inflammation or any positive blood culture for bacteria or fungi)

Use of antibiotics >10 days

Number of red cell transfusions

Number of hypoglycaemic episodes moderate (≤ 2.5 mmol/L), severe (≤ 2.0 mmol/L)

Occurrence of seizures (clinical seizures requiring anticonvulsant therapy)

Paediatric logistic organ dysfunction (PELOD) score[52-54],

Hospital length of stay

Number of children readmitted to PICU within 30 days of trial entry

#### Cost and cost-effectiveness measures

Hospital costs within 30 days of trial entry

Cost per life year (based on 30 days costs and survival)

Hospital and community health service costs within 12 months of trial entry

Cost per life year (based on 12 month costs and survival for all cases)

Cost per disability-free survivor (based on 12 month cost and outcome data for sub group with traumatic brain injury)

#### Follow-up at 12 months

If parents give their consent, all children surviving to hospital discharge will be followed up to 12 months post-randomisation to determine mortality using the NHS Central Register of the Office of National Statistics (ONS). Parents will be informed about the follow-up study at trial entry and asked to give consent. The Trial Manager at the Data Co-ordinating Centre (DCC) will write to parents following discharge home to remind them about the follow-up and ask them to keep the DCC informed about any change of address. At hospital discharge parents will be given a diary to help them record their child's service use post discharge. At around 11 months, following checks with the GP/Health Visitor to determine that this is appropriate, the Trial Manager will send a questionnaire to parents to determine the use of health care resources between discharge and 12 months. Non-responders will be followed-up by letter and telephone.

#### Follow-up of traumatic brain Injury sub-group

TBI is defined for this study as accidental trauma to the head resulting in need for intubation and mechanical ventilation. There are approximately 750 ICU admissions per year in the UK, and an estimated 150 will be recruited into CHiP.

This sub-group is more likely to have longer-term morbidity and parents of children (aged 4 or over) in this sub-group will be asked to provide additional information at 12 months, regarding overall health status, global neurological outcome, attention and behavioural status.

Outcome assessment will comprise four components:

Overall health status: measured by the Health Utilities Index (HUI)

Global neurological outcome: measured by the Kings Outcome Scale for Childhood Head Injury (KOSCHI)

Attention and behavioural assessment: measured by the Child Behavioural Check List (CBCL) and the Connor's Rating Scales revised - short version (CRS-R:S)

The HUI and KOSCHI will be completed using a structured telephone interview (around 10 minutes). The CBCL and CRS are both written questionnaires that will be posted out to the families. They take approximately 30 minutes to complete.

The Health Utilities Index is a multi-attribute health status classification system. Seven attributes (sensation, mobility, emotion, cognition, self-care, pain, fertility) are categorised according to one of 4 or 5 levels. In this population fertility will be excluded. The algorithm (from death to perfect health scale) provides a single numerical value.

KOSCHI is a 5 point categorical scale, ranging from death to normal neurological function, and is similar in structure to the Glasgow Outcome Scale, which is widely used in adult studies. In addition the KOSCHI is further subdivided into two subcategories at points 4 and 5 on the scale (moderate outcome and good outcome). Patient outcomes will be dichotomized between patients in categories 1, 2, 3, 4A and those in 4B, 5A, 5B.

Child behaviour checklist (CBCL/4-18) (problem scales) is based on parental report and assesses problematic child behaviour that is summarised in internalising behaviour (anxious/depressed, withdrawn/depressed, somatic complaints), externalising behaviour (rule-breaking, aggressive) and other (social problems, thought problems, attention problems).

In reference to 1991 normative data (Table 2) Patient outcome can be summarised according to placement within one of the three groups, or according to the T-score.

**Table 2 T2:** Child behavior checklist (CBCL/4-18) assessment of outcome according to T-score

T-score (Whole)	Guideline	T-score (Individual scale)	Guideline
<60	Normal	<65	Normal
60-63	Borderline	65-69	Borderline
>63	Clinical	>69	Clinical

The Conners' rating scales (revised - short version CRS-R:S) assesses symptoms of attention-deficit/hyperactivity disorder and related problem behaviour in children and adolescents based on parent's report.

In reference to 1993 normative data (Table 3) Patient outcome can be summarised according to placement within one of the three groups (marked + moderate, mild + slight, average + good), or according to the T-score.

**Table 3 T3:** The Conner's' rating scales (revised - short version CRS-R:S) assessment of outcome according to T-score

T-score	Guideline
≥ 70	Markedly atypical (significant problem)
66-69	Moderately atypical (significant problem)
61-65	Mildly atypical (possible significant problem)
56-60	Slightly atypical (borderline)
45-55	Average (no concern)
≤ 44	Good

### Adverse events and safety reporting

The Royal Brompton & Harefield NHS Trust, as sponsor of this study, has responsibility to ensure arrangements are in place to record, notify, assess, report, analyse and manage adverse events in order to comply with the UK regulations of Medicines for Human Use (Clinical Trials) Regulations 2004.

All sites involved in the study are expected to inform the Chief Investigator and Study nurse of any serious adverse events/reactions within 24 hours so that appropriate safety reporting procedures can be followed by the Sponsor.

#### Expected side effects

All adverse events judged by either the investigator or the sponsor as having a reasonable suspected causal relationship to insulin therapy qualify as adverse reactions.

Whilst any suspected, unexpected, serious adverse reaction (SUSAR) involving insulin therapy will be reported according to the timelines for SUSARs, expected side effects of insulin will be reported in the annual safety report unless serious enough to warrant expedited reporting.

The most prominent adverse effect of insulin treatment is hypoglycaemia. This is particularly important in the TCG arm of the study which is aiming to control BG within the range 4 - 7 mmol/l which is well above the 2 mmol/l threshold for clinically important hypoglycaemia [55]. The principal measure to avoid clinically important hypoglycaemia will be hourly measurement of BG when insulin is first administered. The insulin administration protocols aim to achieve glucose control with the lowest possible incidence of hypoglycaemia and the avoidance of neuroglycopaenia. Hypoglycaemic events will be reported to the Clinical Co-coordinating Centre and if necessary, the BG control protocols will be revised, whilst still aiming to achieve BG levels within the target ranges.

Insulin is reported to occasionally cause a rash which may be associated with itching.

### Data collection

To minimise the data collection load for busy units, the trial will collaborate with the Paediatric Intensive Care Audit Network (PICANet http://www.picanet.org.uk) to make best use of the established data collection infrastructure which exists in all PICUs in the UK. The PICANet dataset includes most of the items being used in the trial and these data will be transmitted from the participating centres to the Data Co-ordinating Centre electronically using strong encryption. The remaining short term data items will be collected locally by the research nurses, and those for the longer term follow-up will be collected separately by telephone and postal questionnaires. These data will be double entered onto electronic database storage systems at the Data Co-ordinating Centre.

### Economic evaluation

Cost-consequence and cost-effectiveness analyses will be undertaken as part of the proposed study. These economic evaluations will assess whether the costs of achieving tight BG control are justified by subsequent reductions in hospitalisation costs and/or by improvements in patient outcomes. The evaluations will be conducted in two phases, in the first phase all hospital costs at 30 days post randomisation will be compared across treatment groups alongside 30-day outcomes, in the second phase cost and outcomes at 12-months will be compared across the groups.

For the first phase evaluations, detailed resource use data will be collected for each patient enrolled in CHIP using the Paediatric Critical Care Minimum Dataset (PCCMDS)[56] which will be collected by each PICANet unit. Where information on resource use required in CHIP is not available from these sources datasheets similar to those developed as part of the INNOVO study will be used [57]. Information will also be collected on the resources required to achieve tight BG control, in particular all medication use and the staff time involved in monitoring the patients and managing adverse events (e.g. hypoglycaemia) will be noted.

Unit costs for hospital services will be taken from the NHS 'payment by results' database[58]. Where more detailed unit costs are required, for example those associated with staff time and the use of insulin infusion, these will be collected on site visits to centres. Hospital costs up to 30 days will be estimated by valuing each resource use item by the appropriate unit cost.

In the second phase of the study the time horizon of the economic evaluation will be extended to 12 months, and resource use data for hospital re-admissions, outpatient visits and the use of community health services will be collected for all cases. For the sub-sample of patients diagnosed as having traumatic brain injury at study entry, information on the patient's disability at one-year will be collected during telephone interviews with the patients' relatives based on previously developed interview schedules [57]. All community service use will be valued using national unit costs[59]. Total costs for each patient will be calculated by summing the costs of all hospital and community health services used.

All the economic analyses will be based on the treatment groups as randomly allocated ('intention to treat'). The initial analysis will include a cost-consequence analysis and will report mean differences (95% CI) between treatment groups in resource use (e.g. length of hospital stay) and total hospital costs per patient, alongside the primary clinical endpoint. The initial analysis will also combine costs and outcomes at 30 days post-randomisation in a cost-effectiveness analysis, which will report cost per death averted and cost per adverse event averted. The subsequent analysis will use 12-month cost and outcome data to report the cost per death averted for all patients. For the sub-sample of patients diagnosed as having brain injury at study entry, the cost-effectiveness analysis will also report the cost per death or disabled case averted.

The sensitivity analysis will test whether the results are robust to key assumptions made, for example to the choice of unit costs and the time horizon of the analysis. The cost and outcome data collected at one-year will be used to project the impact of the intervention on longer-term costs and outcomes.

### Sample size

A difference of 2 days in the number of ventilator-free days (VFD) within the first 30 days post-randomisation between the two groups has been chosen as the primary outcome measure for the trial. Information from PICANet using data from UK PICUs for 2003-4 estimates that the mean number of VFDs in cardiac patients is 26.7, with a standard deviation (SD) of 4.2. Corresponding figures for non-cardiac patients are a mean of 22.7 days, with a standard deviation (SD) of 6.8 days. As the SD is estimated with error, to be conservative we have assumed the SD is nearer 5.5 days for the cardiac and 8 days for the non-cardiac patients. There are likely to be more non-cardiac than cardiac patients eligible for the trial. We have therefore assumed an overall SD across both cardiac and non-cardiac strata of 7 days. Assuming this is the same in both trial arms, and taking a type I error of 1% (with a 2-sided test), a total sample size of 750 patients would have 90% power to detect this difference. Whereas we can assume minimal loss to follow up to 30 days, there may be some non-compliance (some patients allocated to tight control not receiving this, and some allocated to usual care being managed with tight control). The target size will therefore be inflated to 1000 to take account of possible dilution of effect.

As information from PICANet indicates that there are differences in outcome between cardiac and non-cardiac patients not merely in VFDs but also in 30 day mortality rate (3.4% vs. 20%) and mean duration of time on a ventilator (3.7 vs. 8.0 days, survivors and non-survivors combined), we also wish to be able to detect whether any effect of tight glucose control differs between the cardiac and non-cardiac strata. To have 80% power for an interaction test to be able to detect a difference of two days in the effect of intervention between the strata at the 5% level of statistical significance, we would need to increase the sample size to 1500. If the interaction test was positive this size would allow us to assess the effect of tight glucose control separately in the two strata.

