**Methods/Design:**

The study is an randomised open trial with two parallel groups to assess whether, for children undergoing intensive care in the UK aged ≤ 16 years who are ventilated, have an arterial line in-situ and are receiving vasoactive support following injury, major surgery or in association with critical illness in whom it is anticipated such treatment will be required to continue for at least 12 hours, tight control will increase the numbers of days alive and free of mechanical ventilation at 30 days, and lead to improvement in a range of complications associated with intensive care treatment and be cost effective.

Children in the tight control group will receive insulin by intravenous infusion titrated to maintain BG between 4 and 7.0 mmol/l. Children in the control group will be treated according to a standard current approach to BG management.

Children will be followed up to determine vital status and healthcare resources usage between discharge and 12 months post-randomisation. Information regarding overall health status, global neurological outcome, attention and behavioural status will be sought from a subgroup with traumatic brain injury (TBI).

A difference of 2 days in the number of ventilator-free days within the first 30 days post-randomisation is considered clinically important. Conservatively assuming a standard deviation of a week across both trial arms, a type I error of 1% (2-sided test), and allowing for non-compliance, a total sample size of 1000 patients would have 90% power to detect this difference. To detect effect differences between cardiac and non-cardiac patients, a target sample size of 1500 is required. An economic evaluation will assess whether the costs of achieving tight BG control are justified by subsequent reductions in hospitalisation costs.

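### The non-cardiac SD of 8 and the overall SD of 7 for ventilator-free days do not fit an outcome that scores deaths as 0, so the power stated at N=1000 and for the interaction is probably overstated

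*Protocol article*

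**What the plan says.** Protocol article, Primary outcome: ventilator-free days (VFD) over 30 days, with "VFD = 0 if the child dies before 30 days".

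Protocol article, Sample size: the target is "A difference of 2 days in the number of ventilator-free days (VFD) within the first 30 days post-randomisation between the two groups". From national audit data, "the mean number of VFDs in cardiac patients is 26.7, with a standard deviation (SD) of 4.2". For the non-cardiac stratum the same source gives 22.7 and 6.8. These SDs are then raised: "to be conservative we have assumed the SD is nearer 5.5 days for the cardiac and 8 days for the non-cardiac patients". The single figure used for the main calculation comes next: "We have therefore assumed an overall SD across both cardiac and non-cardiac strata of 7 days". With a two-sided 1% test this gives 750 patients for 90% power, inflated to 1000 for dilution by non-compliance. The target rises to 1500 for 80% power, at the 5% level, to detect a two-day difference in effect between cardiac and non-cardiac children. To justify the interaction test the section cites "30 day mortality rate (3.4% vs. 20%) and mean duration of time on a ventilator (3.7 vs. 8.0 days, survivors and non-survivors combined".

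The Abstract repeats the main claim, after allowing for non-compliance: "a total sample size of 1000 patients would have 90% power to detect this difference".

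**The concern.** An outcome on which a fifth of patients score 0 while the overall mean is 22.7 out of 30 must be widely spread. An SD of 6.8, or 8 after a conservative adjustment, looks too small for that. The stated means are also close to 30 minus the mean ventilator days (30 − 8.0 = 22.0 against 22.7; 30 − 3.7 = 26.3 against 26.7). This suggests that the audit figures may describe time off the ventilator without scoring deaths as 0. The planning variance would then belong to a different outcome from the primary one.

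Two stated claims rest on these SDs: 90% power at 1000 after dilution, and 80% interaction power at 1500, which is the reason given for going to 1500. A null interaction would be read as better-powered evidence of a consistent effect than it is.

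**Working it through.** **Inputs.** Sample size section: means 26.7 and 22.7, audit SDs 4.2 and 6.8, planning SDs 5.5, 8 and 7, mortality 3.4% and 20%, difference 2 days. Recruitment rate section: 1300 cardiac and 1550 non-cardiac eligible per year, so the cardiac share is w = 1300/2850 = 0.456. Equal arms are assumed.

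**Reproducing the plan.**
- Overall SD: √(0.456 × 5.5² + 0.544 × 8²) = 6.97, the stated 7.
- Total N = 4 × 7² × (2.576 + 1.282)² / 2² ≈ 730, close to 750. Power at 750 is 91%.
- Inflating 750 to 1000 allows for a diluted effect of 2 × √(750/1000) = 1.73 days.
- Interaction at 1500 (684 cardiac, 816 non-cardiac): SE = √(4 × 5.5²/684 + 4 × 8²/816) = 0.70, power 81.5%.

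The sample sizes follow from their inputs, so the question is the inputs.

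**Reading A: the stated means already score deaths as 0.** If a share p scores 0 and the overall mean is m, the SD is smallest when all survivors have the same value. The minimum is m × √(p/(1 − p)).
- Non-cardiac: 22.7 × √(0.20/0.80) = 11.35. Both 6.8 and 8 are below it.
- Cardiac: 26.7 × √(0.034/0.966) = 5.01. The audit 4.2 is below it; the planning 5.5 is above it, leaving a survivor SD of √((5.5² − 5.01²)/0.966) ≈ 2.3.

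**Reading B: the stated means and SDs leave deaths unscored (assumption).** Taking them as survivors' means and SDs and adding zeros for deaths gives SD = √((1 − p)s² + p(1 − p)m²).
- Non-cardiac: √(0.8 × 6.8² + 0.16 × 22.7²) = 10.9, with mean 0.8 × 22.7 = 18.2.
- Cardiac: √(0.966 × 4.2² + 0.034 × 0.966 × 26.7²) = 6.4, with mean 0.966 × 26.7 = 25.8.

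**Reading C: as B, but with no spread at all among survivors.** SD = m × √(p(1 − p)): 22.7 × √0.16 = 9.08 and 26.7 × √(0.034 × 0.966) = 4.84. The non-cardiac figure is still above 8.

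**Power.** The within-stratum SD is √(w × SD_c² + (1 − w) × SD_n²). The total SD adds w(1 − w) × (difference in stratum means)² under the root. Main-effect power is Φ(effect/(2 × SD/√N) − 2.576); interaction power is Φ(2/SE − 1.96). Paired figures are for the within-stratum and the total SD.

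| Inputs | SD cardiac / non-cardiac | SD within / total | N=1000, 2 days | N=1000, 1.73 days | N=1500, 2 days | N=1500, 1.73 days | Interaction, N=1500 |
|---|---|---|---|---|---|---|---|
| Plan | 5.5 / 8 | 7 (as stated) | 97% | 91% | – | – | 81.5% |
| A (floors) | 5.01 / 11.35 | 9.03 / 9.25 | 82 / 80% | 68 / 65% | 96 / 95% | 87 / 85% | 62% |
| B | 6.4 / 10.9 | 9.13 / 9.89 | 81 / 73% | 66 / 58% | 95 / 91% | 86 / 79% | 60% |
| C (extreme) | 4.84 / 9.08 | 7.45 / 8.36 | 95 / 89% | 86 / 76% | 99.6 / 98% | 97 / 92% | 78% |

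The interaction SE is 0.882 under A and 0.907 under B. A cardiac share of 40–50% moves the interaction power under A and B only within about 58–64%.

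**The case against.** The strongest reply is that the article does not say how the audit VFDs were scored, so no single corrected power can be fixed. That stands. The floor of 11.35 holds only if 22.7 already counts deaths as 0, and the closeness to 30 minus ventilator days suggests that it may not. The powers under A are therefore not upper bounds across all readings. If 22.7 is set aside and only the 8.0 ventilator days and 20% mortality are used, the non-cardiac floor is (30 − 8.0/0.8) × √(0.2 × 0.8) = 8.0, and the stated powers would largely survive. That minimum is reached only if children who die have no ventilator time and every survivor has exactly 10 days, so it does not make 8 a conservative choice.

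A reader might infer more than the documents support:
- That all the planning SDs are impossible. They are not: the cardiac 5.5 is feasible.
- That the trial is badly underpowered for its main comparison. The recruitment target is 1500, where readings A and B still give 91–96% undiluted and 79–87% diluted.
- That the interaction should be judged after dilution, or the non-cardiac stratum held to a power for 2 days at 1%. The Sample size section applies the inflation only to the step from 750 to 1000 and states no power for a single stratum.

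It is also fair to say that the final confidence intervals will reflect the observed variance whatever was planned. That limits the harm but does not make the stated powers right.

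**Conclusion.** The point holds in this form. If the stated means follow the outcome rule, the audit SDs of 4.2 and 6.8, the non-cardiac planning SD of 8 and the overall SD of 7 are incompatible with the primary outcome. If the stated figures leave deaths unscored, they describe another outcome, and scoring deaths as 0 again takes the non-cardiac SD above 8.

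Under A and B, power at N=1000 is about 73–82% undiluted and 58–68% with the plan's own dilution; the stated 90% is the diluted claim. Interaction power at N=1500 is about 60–62% against the stated 80%. With no survivor spread (C) the figures are 89–95%, 76–86% and 78%, still short of the two stated claims. The damage is mainly to the N=1000 claim and to the interaction claim that justifies 1500.

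This rests on the 1300:1550 mix, equal arms, normal approximations and, for B and C, the assumption that the stated means (for B, also the SDs) apply to survivors.

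**What to change.** Recompute the mean and SD of VFD in each stratum from the same audit data with deaths before day 30 scored 0. Replace 26.7/4.2, 22.7/6.8 and the assumed 5.5, 8 and 7. In the Sample size section and the Abstract, restate the main-effect power at 1000 and at 1500, saying whether dilution is included, and the interaction power at 1500. Alternatively, give the interaction detectable with 80% power: (1.96 + 0.842) × 0.882 ≈ 2.5 days under A, and (1.96 + 0.842) × 0.907 ≈ 2.5 days under B, rather than 2.

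The cost is one audit query and a reworded paragraph, with no change to N, outcome or recruitment. The drawback is that the stated power becomes less favourable.

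### The 1500 target for the cardiac/non-cardiac interaction carries no dilution allowance, although the main-effect target does; with the same allowance, interaction power is about 67–70% rather than 80%

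*Protocol article*

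**What the plan says.** The Sample size section makes two calculations in consecutive paragraphs.

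- **Main effect.** A two-day difference in ventilator-free days, an SD of 7, two-sided 1% error and 90% power give 750 patients. The text then allows for patients in either arm not being managed as allocated: "The target size will therefore be inflated to 1000 to take account of possible dilution of effect".
- **Interaction.** The size is set so that a test with 80% power is meant "to be able to detect a difference of two days in the effect of intervention between the strata". The significance level is 5%, and on that basis the text says "we would need to increase the sample size to 1500". This paragraph does not mention non-compliance or dilution.

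On variability, the section sets the audit SDs aside: "we have assumed the SD is nearer 5.5 days for the cardiac and 8 days for the non-cardiac patients". It continues: "We have therefore assumed an overall SD across both cardiac and non-cardiac strata of 7 days".

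The abstract shows the same split. It ties the non-compliance allowance to the 1000 and then says only: "To detect effect differences between cardiac and non-cardiac patients, a target sample size of 1500 is required". It gives no power, significance level or effect size for the interaction.

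**The concern.** The interaction is the difference between two stratum-specific treatment effects. The Type of analysis section specifies intention to treat, so crossover that shrinks the overall effect also shrinks the effect in each stratum. If it does so equally in both, the interaction shrinks by the same factor. A plan that treats two days as the effect before dilution in one paragraph should treat two days the same way in the next, or say that the meaning has changed.

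What is at stake is how the interaction test is justified and read. It is the only reason given for going from 1000 to 1500. If the real chance of missing a two-day interaction is nearer one in three than one in five, a null result is weaker evidence of a common effect than the stated 80% suggests.

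**Working it through.** **Inputs from the Sample size section:** difference of 2 days for both the main effect and the interaction; overall SD 7; stratum SDs 5.5 (cardiac) and 8 (non-cardiac); main test at 1%, two-sided, 90% power; interaction test at 5%, 80% power; totals 750, 1000 and 1500; minimal loss to follow-up, taken as zero.

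**Input from the Recruitment rate section:** 1300 cardiac and 1550 non-cardiac eligible patients per year, so 45.6% cardiac.

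**Assumptions:** 1:1 allocation within strata; a two-sided interaction test (the text gives no sidedness); normal approximation.

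**Step 1: main effect.** n per arm = 2 × (2.576 + 1.282)² × 7² / 2² ≈ 365, or 730 in total, against 750 stated. Power at 750 is 90.9%, so the plan's figure is reproduced.

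**Step 2: implied dilution.** Required N varies as 1/effect². Going from 750 to 1000 therefore implies a retained fraction of √(750/1000) = 0.866, so 2 days becomes 1.73 days. Check: power at 1000 for 1.73 days is again 90.9%.

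**Step 3: interaction at 1500, no dilution.** With 684 cardiac and 816 non-cardiac patients, SE = √(4·s₁²/684 + 4·s₂²/816) and power = Φ(d/SE − 1.96).

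- SDs 5.5 and 8: SE = √(121/684 + 256/816) = 0.700; power = Φ(2/0.700 − 1.96) = 81.5%.
- Common SD 7: SE = √(196/684 + 196/816) = 0.726; power = Φ(2/0.726 − 1.96) = 78.7%.

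The total needed for exactly 80% is 1445 and 1551 respectively. So 1500 is the undiluted figure, with no room left for an allowance.

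**Step 4: interaction at 1500 with the Step 2 factor.** The same SEs are used, with d = 1.73. Results for an even split of strata are added.

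| SDs | Split | Power, 2 days | Power, 1.73 days | N for 80%, diluted |
|---|---|---|---|---|
| 5.5 / 8 | 1300:1550 | 81.5% | 69.6% | 1926 |
| 7 / 7 | 1300:1550 | 78.7% | 66.5% | 2068 |
| 5.5 / 8 | 50:50 | 80.5% | 68.6% | 1973 |
| 7 / 7 | 50:50 | 79.0% | 66.9% | 2052 |

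**Step 5: what 80% power at 1500 does cover.** The detectable intention-to-treat difference is (1.96 + 0.842) × SE, which is 1.96 days (SE 0.700) or 2.03 days (SE 0.726), so about two days. Under full compliance, two days after dilution corresponds to 2/0.866 = 2.3 days.

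**The case against.** **The stated figure is not miscalculated.** Taken alone, 80% power for two days at 1500 is correct to within two percentage points. This stands. The fault is that an allowance made in one calculation was not carried to the next.

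**The dilution factor is not the plan's own number.** The plan gives no non-compliance rate and speaks only of possible dilution. The 0.866 is inferred from two rounded totals, and equal dilution in the strata is an assumption. Unequal compliance could shrink or enlarge the interaction. This also stands, and 67–70% must be labelled as a scenario. It is, however, the scenario that the plan's own inflation implies.

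**The two days may already be the intention-to-treat difference.** On that reading 1500 is right. The text does not say so, and for the main effect it treats the same two days as undiluted. The reading is open to the sponsor but has to be written down.

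**A one-sided test would rescue the number.** With dilution, SDs 5.5 and 8 and a one-sided 5% test, 1517 patients would do. But no direction of interaction is stated, the main test is two-sided, and dilution is not mentioned for the 1500.

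**The SDs are already conservative.** With the audit SDs of 4.2 and 6.8, diluted power at 1500 would be about 85%. The shortfall therefore appears only with both cautions applied together. But the plan adopts the larger SDs because the SD is estimated with error, which is a different reason, and it applies both cautions to the main effect.

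**Stronger readings.** A reader might infer that the trial is underpowered for its primary question; it is not, since 1500 exceeds the dilution-adjusted 1000. A reader might also infer that the interaction test decides whether the strata are reported separately. The Sample size section says only what a positive test would permit, and the Type of analysis section lists the cardiac versus non-cardiac subgroup analysis without condition. Nor does any passage say that a negative test will be read as proof of a common effect.

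**Conclusion.** The inconsistency is real. The main-effect size allows for dilution; the interaction size does not. Under the allowance implied by 750 to 1000, two-sided interaction power at 1500 is about 67–70%, so the chance of missing a two-day interaction is roughly 30–33% instead of 20%. Reaching 80% would take about 1930 to 2070 patients.

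This rests on four assumptions: a back-calculated factor of about 0.87, equal dilution in both strata, a two-sided test, and two days meaning the effect before dilution, as it does for the main effect. Severity is moderate to minor: what is affected is the stated power and the interpretation of one interaction test, not the primary comparison.

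**What to change.** Keep 1500. In the Sample size section, do one of the following:

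- restate the interaction power at 1500 as about 67–70% under the same dilution allowance as the main effect, giving the factor and the assumption that it is equal in both strata; or
- state that 80% power at 1500 refers to a two-day intention-to-treat difference, already diluted, and that this corresponds to about 2.3 days under full compliance. The 2.3 must carry that label, because the detectable intention-to-treat difference remains about two days.

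State in either case that the interaction test is two-sided, if that is what is meant. The abstract gives no interaction power, so it needs at most a note that the 1500 includes no non-compliance allowance for the interaction.

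The cost is one recalculation and a sentence or two. Recruitment, conduct and the primary analysis do not change; under the first option the stated interaction power becomes less favourable.
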